### Treatment

A standardised Panax ginseng C.A Meyer (Araliaceae; Asian ginseng or *Renshen*) root extract will be used as treatment. The ginseng and matching placebo (i.e. identical appearance, taste and odour) will be dispensed as 100 mg gel-filled soft capsules for oral intake twice daily, for a total of 24 weeks. The standardised ginseng extract and matching lactose-based placebo will be manufactured in accordance with good manufacturing practice (GMP) by Ginsana SA, Switzerland. The ginseng extract will be standardised to contain 4% ginsenosides. Routine quality control checks will be undertaken on the packaging and contents of the batch to ensure stability and quality with handling and storage also following GMP procedures. The dosage of ginseng was determined by referencing previous clinical trials for the same indication [22,23], and by recommendations from the manufacturer. This product is listed for use as an herbal medicine with the TGA Australia (ARTG 14987).

Throughout the trial, participants will be supplied with symptomatic relief medication, a short acting beta2-agonist Salbutamol, to be used on an as needed basis. To monitor medication compliance, participants will be required to document such use in a take home diary. Participants will be asked to return any capsules they have neglected to take so that these can be checked against the diary entries.

Participants will be advised not to take certain COPD medications throughout the trial. Such as; short acting anti-cholinergics, long acting beta2-agonists, theophylline, inhaled corticosteroids (ICS) and combination ICS/beta2-agonists. ICS are recommended for more advanced COPD sufferers and those with repeated exacerbations [1]. The use of a long acting anti-cholinergics will be allowed.

If exacerbations occur, management will be decided by the patients' own physician/healthcare provider and all relevant details including medications will be recorded by the research investigators as secondary outcomes. The trial defines exacerbations as at least a 2-day persistence of at least two major symptoms, such as worsening dyspnoea and an increase in sputum purulence, volume, or both, or of any single major symptom plus more than one minor symptom (upper airway infection, unexplained fever, increased wheezing) [24].

### Outcomes

The primary outcome measures will be QoL improvement assessed by using three validated and self-administered questionnaires.

• St Georges Respiratory Questionnaire (SGRQ)

• Short Form Health Survey (SF-36); and

• COPD Assessment Test (CAT)

Participants will complete the three questionnaires at each visit, 6 times in total (Week 0, 4, 16, 28, 40 and 52). (Table 1)

**Table 1 T1:** Measurements to be taken throughout the trial

Visit/Week	1/0	2/4	3/16	4/28	5/40	6/52
**SGRQ**	✓	✓	✓	✓	✓	✓

**SF-36**	✓	✓	✓	✓	✓	✓

**CAT**	✓	✓	✓	✓	✓	✓

**Spirometry**	✓	✓	✓	✓	✓	✓

**Full Blood Count**	✓(Including alpha_1 _antitrypsin)			✓		

**Blood Biochemistry** **KI & LR function**	✓			✓		

CAT: COPD Assessment Test; KI: Kidney; LR: Liver; SF-36: Short Form Health Survey; SGRQ: St Georges Respiratory Questionnaire.

Secondary outcome measures include efficacy and safety components.

Lung function using spirometry indices of FEV_1 _and FEV_1_/FVC ratio.

Use of relief medication short-acting bronchodilator (beta2-agonist Salbutamol)

Frequency, nature and severity of exacerbations

Emergency department presentations and medical practitioner visits

Full blood examination and blood biochemistry for liver and renal function

Adverse event reporting

Spirometry at each site will be conducted using SpiroUSB™ (CareFusion) and Spida5^® ^software. Routine calibration and standard operating procedures will be uniformly undertaken at each site. Participants will be asked to perform spirometry at each visit, 6 times in total (Week 0, 4, 16, 28, 40 and 52). Participants will be advised not to use respiratory medications for several hours prior to their spirometry testing. Two sets of measurements will be taken at each visit, pre-bronchodilator and post-bronchodilator (post 400 μg of inhaled Salbutamol).

Any adverse events will be listed in the trial record and followed-up to completion by the trial co-ordinators and respiratory physicians. Adverse event details will be scored using a six-point scale, 0 = none, 1 = minimal, 2 = mild, 3 = moderate, 4 = severe, and 5 = extremely severe. Participants will be able to report adverse events anytime throughout the trial and will receive advice accordingly. Serious adverse events will be reported to the reviewing HREC and site HRECs within the timeframe specified by the lead HREC.

Throughout the study period (52 weeks) trial coordinators will contact the participant's usual treating doctor to record relevant data on presentations and exacerbations.

To assist with outcome documentation and medication compliance, participants will be given a participant diary to complete on a daily basis for the duration of the trial. They will be asked to record trial medication and relief medication usage as well as any new medications they commence during the trial.

Participants may withdraw from the study for any reason at any time without repercussion. They will only be withdrawn by investigators if it is deemed medically unsafe for them to continue. Dropouts will not be replaced.

### Statistical analysis

The trial data will be analysed by an independent biostatistician who will be blinded to the subject allocation. Primary outcome measures SGRQ, SF-36 and CAT scores of participants in the treatment and placebo groups will be assessed at baseline, start of treatment (4 weeks) mid-treatment (16 weeks), end of treatment (28 weeks), mid follow-up (40 weeks) and at the end of follow-up (52 weeks). A suitable statistical package such as SAS will be used to analyse the data. An intention-to-treat analysis will be applied using the Last Observation Carried Forward (LOCF) method. Analysis of covariance with baseline as covariate will be used to assess differences in treatment outcomes between the two groups at each of these time points. To correct for inflated risk of Type 1 error, multiple comparison procedures suggested by Ludbrook et al will be used [25,26]. The use of relief medication during the trial will be investigated for its effect on the outcome measures by using it as a covariate in the statistical analysis. A Data Safety Monitoring Board has been established to assess the progress of the trial, particularly safety endpoints.

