## Objective

The objective of this study is to evaluate the therapeutic value and safety profile of a standardised root extract of Panax ginseng C.A Meyer (ginseng) for symptomatic relief, with a focus on QoL improvement in individuals with moderate (GOLD Stage II) COPD (FEV_1_/FVC < 0.7 and FEV_1 _50% - 80% predicted). To fulfil the objective, answers to the following questions will be addressed 1) Does a standardised extract of ginseng produce beneficial effects/symptomatic relief in subjects with moderate COPD, in terms of improved QoL and/or improved respiratory function? 2) Does standardised ginseng extract reduce the use of conventional symptom-relief medication in subjects with moderate COPD? 3) With six months treatment and six months follow-up, what are the time courses of onset and persistence of any beneficial effects of the ginseng extract in subjects with moderate COPD? 4) What adverse events does the ginseng extract produce in subjects with moderate COPD?

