## Methods

### Design

This study is a randomised, multi-centre, double-blind, placebo-controlled, two-armed parallel clinical trial, comparing a standardised ginseng extract to placebo. The design of the study will integrate rigorous, contemporary clinical research methodology in accord with principles set out in the Declaration of Helsinki and the Good Clinical Practice guidelines with the theory that guides the appropriate use of traditional Chinese medicine in clinical practice. Reporting will be guided by the CONSORT statement [18,19], including relevant intervention extensions relating to herbal medicines [20].

Two hospitals in Melbourne, Australia will randomly assign 168 patients with moderate COPD at a ratio of 1:1 into the ginseng group or matching placebo. Consenting eligible participants will be enrolled for 52 weeks and will be required to attend 6 visits in total. The trial is designed in three phases, 4 weeks run-in; to ensure participants are clinically stable with respect to their COPD, 24 weeks treatment; with either ginseng or placebo capsules, and 24 weeks follow-up (Figure 1).

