### Sample size

The sample size calculation is based on the effect size on QoL changes in COPD subjects, in a RCT of one of the most commonly used long-acting beta_2_-adrenoceptor agonists (salmeterol) [21]. In the study, the mean score change on the St Georges Respiratory Questionnaire (SGRQ) was significantly higher (*p *< 0.05) in the treatment group (-6.8 ± 13.2) than in the placebo group (-1.4 ± 11.7) [21]. For the proposed study, to achieve a similar difference between the ginseng extract and placebo treatment groups with an 80% power and a two-tailed significance level of 5%, it is estimated that a sample size of 84 subjects per group will be required, that is, 168 in total. Intention-to-treat analysis will be applied to minimise bias due to drop-outs.

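### LOCF, the only missing-data method named, carries on-treatment scores into the off-treatment visits, so it cannot validly answer the persistence question

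*Protocol article*

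**What the plan says.** The Statistical analysis section of the protocol article fixes how missing scores are handled: "An intention-to-treat analysis will be applied using the Last Observation Carried Forward (LOCF) method". No other method is named. In the same section, the comparison made at every scheduled visit is set by the sentence that begins "Analysis of covariance with baseline as covariate will be used to assess differences in treatment outcomes between the two groups at each of these time". The visits after baseline are described as "start of treatment (4 weeks) mid-treatment (16 weeks), end of treatment (28 weeks") and then "mid follow-up (40 weeks) and at the end of follow-up (52 weeks").

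The Design section gives the phases that follow the 4-week run-in: "24 weeks treatment; with either ginseng or placebo capsules, and 24 weeks follow-up". Weeks 0 and 4 therefore come before any treatment effect, Weeks 16 and 28 are on treatment, and Weeks 40 and 52 are off treatment.

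The third research question in the Objective section is: "With six months treatment and six months follow-up, what are the time courses of onset and persistence of any beneficial effects". The Sample size section adds: "Intention-to-treat analysis will be applied to minimise bias due to drop-outs". Drop-outs are not replaced, and no drop-out rate is given.

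**The concern.** The trial asks when a benefit starts and whether it lasts once capsules stop. LOCF fills a missing visit with the last score seen, whichever phase that score came from. Two crossings follow from the visit schedule:

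- **Treatment into follow-up.** A participant last seen at Week 16 or 28 supplies an on-treatment score at Weeks 40 and 52. If the effect has faded by then, the analysis counts a persistence that nobody observed.
- **Run-in into treatment.** A participant last seen at Week 4 supplies a pre-treatment score at Weeks 16 and 28. In expectation such participants contribute no difference between the arms.

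At stake are the answer to the persistence question and, to a lesser degree, the meaning of the end-of-treatment difference. The rule is stated in the article, so it is not a detail left to a document that is not shown.

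**Working it through.** **Inputs from the Sample size section.** SGRQ change −6.8 (SD 13.2) on active treatment and −1.4 (SD 11.7) on placebo; 80% power; two-sided 5%; 84 per group.

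**The plan's own figure.** Difference = 6.8 − 1.4 = 5.4. Pooled SD = √[(13.2² + 11.7²)/2] = √155.565 = 12.47. Then n per group = 2 × (1.960 + 0.842)² × 155.565 / 5.4² = 83.8, rounded up to 84, with power 80.1%. The stated size reproduces, and it contains no allowance for drop-out.

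**Assumptions.** Drop-out rates are not in the article, so a range is used. Unless stated otherwise, drop-out is random and equal in the two arms, and the effect is 5.4 at both Week 16 and Week 28.

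**Week 52, effect gone after treatment.** Participants last seen at Week 16 or 28 carry the 5.4-point difference; everyone else shows none.

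False difference = share last seen on treatment × 5.4

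| Share last seen on treatment | False difference at Week 52 | Rejection rate (nominal 5%) |
|---|---|---|
| 10% | 0.54 | 5.9% |
| 20% | 1.08 | 8.7% |
| 30% | 1.62 | 13.4% |

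The rejection rates use a standard error of 12.47 × √(2/84) = 1.92.

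**Week 52 with a constant loss per visit.** With 8% lost before each visit after Week 4:

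- last seen at Week 16: 0.92 × 0.08 = 7.36%
- last seen at Week 28: 0.92² × 0.08 = 6.77%
- last seen on treatment: 14.13%, so the false difference is 0.1413 × 5.4 = 0.76

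Simulated trials (84 per arm, score SD 16 assumed, change SD 12.47, analysis of covariance on LOCF data) gave 0.77, with 7.1% rejection. With 5% per visit the share is 0.95 × 0.05 + 0.95² × 0.05 = 9.26%, giving 0.50.

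**Week 52, effect fully persistent.** Only participants last seen at Week 4 lack the effect. At 8% per visit LOCF gives 0.92 × 5.4 = 4.97 (4.94 in simulation), an understatement.

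**Week 28, equal loss.** At 8% per visit the 8% last seen at Week 4 contribute no difference, so LOCF gives 0.92 × 5.4 = 4.97, as in simulation. At 5% per visit it gives 5.13. Both are compared with 5.4, the effect had all stayed on treatment.

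**Week 28, unequal loss.** Suppose there is no true effect, both arms change by the same 4 points, and 30% of ginseng and 10% of placebo participants are last seen at Week 4.

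- Both arms improve (−4): 0.7 × (−4) − 0.9 × (−4) = +0.8, a false difference against ginseng.
- Both arms worsen (+4): 0.7 × 4 − 0.9 × 4 = −0.8, a false difference in its favour.

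**The case against.** The strongest defence is that the damage is limited and partly a matter of definition. Much of that stands.

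- **Standard errors.** A reader might infer that single imputation makes the standard errors invalid. That is not supported here. Each visit has its own analysis of covariance with one value per person. In the 8% scenario the model standard error matched the empirical one (1.72 against 1.72). The problem is what is estimated.
- **Who carries what.** A reader might infer that everyone lost after Week 28 carries the end-of-treatment score. Someone last seen at Week 40 carries an off-treatment score to Week 52. The relevant share is those last seen at Week 16 or 28.
- **Direction.** A reader might infer that LOCF always favours persistence. It does so only if the effect fades. It understates a lasting effect, and with no effect at any time and equal random drop-out it is unbiased.
- **Week 28.** Whether the effect is diluted depends on the target. Suppose drop-out is 10% in each arm and drop-outs would have had the placebo mean. LOCF then gives 0.9 × 5.4 = 4.86, which equals the difference regardless of adherence. That agreement fails when drop-out is unequal. With 30% of ginseng and 10% of placebo participants lost, LOCF gives a difference of 0.7 × 6.8 − 0.9 × 1.4 = 3.50, against 0.7 × 5.4 = 3.78. Nor did LOCF cost power in the 8% scenario: 82%, against 79% for observed data.
- **Size.** About 0.8 points at Week 52 is under half a standard error. The scenario assumes random drop-out, which suits an observed-data analysis, so it does not rank the methods under informative drop-out.
- **Wording.** The Sample size section credits intention-to-treat, not LOCF, with limiting drop-out bias. The article does not label LOCF primary; it is simply the only method named. A condensed article's silence on sensitivity analyses is not a fault.

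None of this answers the central point. A score taken on treatment is not evidence about the state 12 or 24 weeks after treatment ended.

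**Conclusion.** The point holds for the persistence question and, in weaker form, for Week 28. If the benefit fades, LOCF reports a false Week 52 difference of 0.54 to 1.62 SGRQ points when 10% to 30% are last seen on treatment, and about 0.8 points with 8% random loss per visit. If the benefit lasts, the same rule understates it, at about 5.0 instead of 5.4. The Week 52 analysis therefore mixes observed follow-up with carried treatment-period scores, in a proportion set by drop-out.

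At Week 28 the shrinkage to about 5.0 is relative to the effect had all stayed on treatment; with unequal drop-out the bias can go either way. All these sizes rest on assumed drop-out rates and on the planned 5.4-point effect. The mechanism itself rests only on the stated method and the visit schedule.

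**What to change.** In the Statistical analysis section, replace LOCF as the main method with a likelihood-based mixed model for repeated measures, or multiple imputation, using all observed visits of all randomised participants. The model should include treatment, visit, treatment-by-visit, baseline score and site (the randomisation is stratified by site), and report the group contrast at each visit. Week 40 and 52 contrasts then use the follow-up scores actually observed, with earlier visits informing the missing ones through the model.

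Keep LOCF at most as a sensitivity analysis, with the rule that no value is carried across Week 28 into follow-up. Add one sensitivity analysis that lets data be missing not at random.

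The cost is revised wording and some programming, with no extra visits or participants. The downside is that the model assumes data are missing at random, which the added sensitivity analysis probes, and that estimates may be slightly less precise than under LOCF. The change should be made before unblinding.

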#### Exclusion criteria

1) current smokers; 2) individuals with a diagnosis of alpha_1_-antitrypsin deficiency; 3) a history of asthma or chronic systemic infections or inflammatory conditions in the last three months; 4) pregnancy, breast-feeding or women intending to become pregnant during the course of the study; 5) serious illnesses such as heart, liver or kidney diseases; 6) those who are unable to adequately perform spirometry tests; 7) those taking long-term immunosuppressive agents or immunostimulants; 8) those who have an allergic history to ginseng products; 9) those currently using a ginseng-containing product or have used a ginseng product within the last three months; 10) those who are current users of anticoagulants, anti-hyperglycaemics or monoamine oxidase inhibitor anti-depressants; and 11) those who have undertaken pulmonary rehabilitation within three months of the commencement of the study, or intend to enter pulmonary rehabilitation during the study.

Preliminary screening for eligibility will be undertaken at Visit 1 and during the 4-week run-in period. After this period if suitability continues, participants will be randomly assigned to one of the two treatment groups, ginseng or matching placebo. Continued suitability requires that they be clinically stable and not have experienced an acute infective exacerbation of COPD during the run-in period and that post-bronchodilator spirometry values stay within the moderate (Stage II) range. Individuals who do not meet the preliminary criteria will not be randomised and their participation in the trial will be discontinued. Participants' self-reported respiratory symptoms, smoking status, current medications and other medical conditions will be documented at baseline and throughout.

As well as a conventional diagnosis of COPD performed by a physician, participants must also meet the appropriate Chinese medicine syndrome classifications of Lung Qi deficiency or Lung and Spleen Qi deficiency. A registered Chinese medicine practitioner will perform this diagnosis and only those with either of the two syndromes will be accepted into the study.

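### The planned ANCOVA tests two visits that precede treatment and, by elimination, adjusts for the Week 0 screening score instead of the last score before treatment

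*Protocol article*

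**What the plan says.** The Statistical analysis section states that the three questionnaire scores "will be assessed at baseline, start of treatment (4 weeks) mid-treatment (16 weeks), end of treatment (28 weeks"), and then at 40 and 52 weeks. That makes six points, with baseline and the Week 4 start of treatment as separate entries. ANCOVA with baseline as covariate is to be "used to assess differences in treatment outcomes between the two groups at each of these time points". A multiple-comparison correction is planned by reference to cited sources; the article states neither the procedure in use nor the family of tests.

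The Outcomes section and Table 1 give six visits, at Weeks 0, 4, 16, 28, 40 and 52. All three questionnaires and spirometry are done at every one. The Design section sets the order as 4 weeks of run-in, 24 weeks of treatment and 24 weeks of follow-up. The text under Exclusion criteria makes Visit 1 and the run-in the screening period, and continues: "After this period if suitability continues, participants will be randomly assigned to one of the two treatment groups".

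**The concern.** Read as written, the rule asks for a between-arm test at two visits where no treatment effect can exist. It also adjusts the later comparisons for a score taken four weeks before treatment starts, when a more recent pre-treatment score is available for every randomised participant who completes the Week 4 questionnaires.

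Two things are at stake. The first is precision: change during the run-in that persists to later visits is left in the residual, and chance imbalance at the point of randomisation is adjusted for only in part. The second is that comparisons with no information may be counted in the multiplicity correction, at the expense of those that matter. In addition, the article never names the baseline visit outright, so the covariate should be fixed before the data are unblinded.

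**Working it through.** **1. Which visit is baseline?** Six analysis points are listed and six visits are scheduled. Matching them:

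| Listed point | Week | Relation to treatment |
|---|---|---|
| Baseline | 0 (by elimination) | Screening, before run-in and randomisation |
| Start of treatment | 4 | After run-in, before any treatment effect |
| Mid-treatment | 16 | On treatment |
| End of treatment | 28 | On treatment |
| Mid follow-up | 40 | After treatment |
| End of follow-up | 52 | After treatment |

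Baseline cannot be Week 4, because Week 4 has its own entry. If Week 4 were nevertheless meant, the Week 4 test would become the degenerate one, and two of the six points would still precede treatment.

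**2. What the model gives at Weeks 0 and 4.** For participant i, the ANCOVA at visit t is Y_t,i = a + b × Baseline_i + c × Arm_i + error_i. At Week 0, Y_t is Baseline. The fit is exact with b = 1 and c = 0, the residual variance is zero, and there is no usable test. At Week 4, Y_t was recorded before treatment could act, so the true c is zero and any difference is chance.

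**3. The plan's own sample size.** Inputs from the Sample size section: SGRQ changes of -6.8 (SD 13.2) and -1.4 (SD 11.7), two-sided 5%, 80% power.

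- Difference: 6.8 - 1.4 = 5.4.
- Pooled SD: √((13.2² + 11.7²)/2) = √155.565 = 12.47.
- n per arm = 2 × 155.565 × (1.960 + 0.842)² / 5.4² = 83.7, rounded up to 84.

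This agrees with the stated figure, "a sample size of 84 subjects per group will be required, that is, 168 in total". It is a single unadjusted comparison, so it contains no allowance for a multiplicity correction.

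**4. Precision (correlations assumed; none are in the documents).** ANCOVA residual variance is proportional to 1 - r², where r is the correlation of the covariate with the later score. The ratio for Week 0 against Week 4 is (1 - r0²)/(1 - r4²).

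| r4 | r0 = r4 | r0 = r4 - 0.05 | r0 = r4 - 0.10 |
|---|---|---|---|
| 0.6 | 1.00 | 0.6975/0.64 = 1.09 | 0.75/0.64 = 1.17 |
| 0.7 | 1.00 | 0.5775/0.51 = 1.13 | 0.64/0.51 = 1.25 |
| 0.8 | 1.00 | 0.4375/0.36 = 1.22 | 0.51/0.36 = 1.42 |

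The range is 1.00 to 1.42.

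**5. Multiplicity (Bonferroni and one score per questionnaire assumed).** With 84 per arm, the standard error is 12.47 × √(2/84) = 1.925, the noncentrality is 5.4/1.925 = 2.806, and there are 166 degrees of freedom. Two-sided noncentral-t power:

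| Tests in the family | Per-test alpha | Power for 5.4 points |
|---|---|---|
| 12 (3 questionnaires × Weeks 16, 28, 40, 52) | 0.05/12 = 0.0042 | 46.3% |
| 15 (Week 4 added) | 0.05/15 = 0.0033 | 43.4% |
| 18 (Weeks 0 and 4 added) | 0.05/18 = 0.0028 | 41.2% |

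The relevant comparison is 12 against 15, because the Week 0 model yields no p-value that could enter a correction.

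**The case against.** The strongest reply is that this is loose wording with little consequence. Much of that stands.

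- **No bias.** Week 0 and Week 4 scores both precede randomisation, so either is a valid covariate. A Week 0 score that correlates with Week 4 also adjusts for a good part of any chance imbalance at randomisation. A reader might infer that the treatment estimate is distorted or that imbalance goes unadjusted; the documents support neither.
- **The precision loss may be nil.** Participants must be clinically stable and stay within the Stage II range through the run-in, so the two scores may predict later scores almost equally well. With equal correlations nothing is lost.
- **The multiplicity cost is conditional.** It is tempting to say that six of 18 comparisons are wasted. But three of those six are degenerate and produce no test. The article also defines neither the procedure nor the family, which it may properly leave to an analysis plan. A step-down method would cost less than Bonferroni, and a family limited to visits after treatment starts would cost nothing.
- **Week 4 is labelled.** The section itself calls it the start of treatment, so a chance difference there is unlikely to be read as a treatment effect.

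A further tempting inference is that Week 0 scores were taken while participants were still on medicines they later had to stop. The Treatment section says only: "Participants will be advised not to take certain COPD medications throughout the trial". It gives no stop date relative to Visit 1, and the Design section gives the purpose of the run-in as confirming stability. The point does not rely on this.

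The reply does not remove the stated rule. The article specifies the covariate and the time points, and as specified they include two uninformative comparisons and, by elimination, the older of two available pre-treatment scores.

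**Conclusion.** The point holds as a matter of efficiency and clarity. That Week 0 and Week 4 comparisons cannot show a treatment effect follows from the schedule alone and needs no assumption. That baseline means Week 0 is an inference by elimination, though a firm one.

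The sizes are conditional. Residual variance with the Week 0 covariate is between 1.00 and 1.42 times that with Week 4 over the assumed correlations. Power for 5.4 SGRQ points falls by about 3 percentage points (46% to 43%) only if the correction is Bonferroni, each questionnaire contributes one score, and the Week 4 tests are in the family; it does not fall at all if they are excluded. Nothing here shows a biased treatment effect or an error in the sample size arithmetic.

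**What to change.** In the Statistical analysis section:

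1. Name the baseline visit. Define it as the Week 4 score, the last before treatment, for the three questionnaires and for spirometry. Alternatively, enter the Week 0 and Week 4 scores jointly as covariates.
2. Restrict between-arm tests, and the family for the multiplicity correction, to Weeks 16, 28, 40 and 52.
3. Report Weeks 0 and 4 by arm descriptively, without tests.

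The Week 4 measurements are already scheduled in Table 1, so the change is to wording only, with no extra visits or participants. It should be made before unblinding so that the choice of baseline cannot depend on the results.

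### Question 3 asks about onset and persistence, but the stated analysis compares the arms visit by visit and never estimates how the treatment effect changes between visits

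*Protocol article*

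**What the plan says.** The Objective section of the protocol article lists four questions. The third asks, over six months of treatment and six months of follow-up, "what are the time courses of onset and persistence of any beneficial effects of the ginseng extract in subjects with moderate COPD".

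The visits are at Weeks 0, 4, 16, 28, 40 and 52. Treatment runs from Week 4 to Week 28, so Weeks 16 and 28 are on treatment and Weeks 40 and 52 are off it.

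The Statistical analysis section names a single between-group method, ANCOVA adjusted for baseline, whose stated purpose is to "assess differences in treatment outcomes between the two groups at each of these time points". It adds a rule for missing data ("An intention-to-treat analysis will be applied using the Last Observation Carried Forward (LOCF) method"), a multiplicity step ("To correct for inflated risk of Type 1 error, multiple comparison procedures suggested by Ludbrook et al will be used") and relief medication as a covariate. It names no treatment-by-visit term, no repeated-measures model and no contrast between visits, and it does not say what result would count as onset or persistence.

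**The concern.** A time course has two parts. One is whether a benefit over placebo exists at a given visit. The other is whether the benefit at one visit is larger or smaller than at another: does it build up from Week 16 to Week 28, and does it fade from Week 28 to Weeks 40 and 52? The stated ANCOVA covers only the first part. A significant result at Week 28 with a non-significant one at Week 52 is not evidence that the effect fell, and a non-significant Week 16 followed by a significant Week 28 is not evidence of slow onset. Two separate confidence intervals do not supply the missing estimate either, because the visit effects come from the same patients and are correlated.

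At stake is the reporting of one of the four study questions, the one that the 24-week off-treatment follow-up mainly serves. Without an estimate of change, a steady effect could be described as delayed or lost, and a partly retained effect as gone.

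**Working it through.** **Inputs.** From the Sample size section: SGRQ mean changes of -6.8 (SD 13.2) and -1.4 (SD 11.7), 84 per group, 80% power, two-sided 5%. From the Statistical analysis section: four visits after treatment starts (Weeks 16, 28, 40, 52).

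**Assumptions, not in the article.** The planning SD applies at every visit. The correlation ρ between the estimated treatment effects at any two visits is common to all pairs and is varied from 0.3 to 0.9. The multiplicity procedure is cited without being described, so Bonferroni over four visits stands in for it.

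**The plan's own figure.** Difference = 6.8 - 1.4 = 5.4. Pooled SD = √((13.2² + 11.7²)/2) = √155.565 = 12.47. n per group = 2 × (1.960 + 0.842)² × 155.565 / 5.4² = 83.8, rounded up to 84. The stated sample size reproduces; it is for a single between-arm comparison.

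**Precision at one visit.** SE = 12.47 × √(2/84) = 1.92. Standardised effect = 5.4 / 1.92 = 2.81. Power is about 80% at 5%, and about 62% at 5%/4. If only half the effect is present (2.7 points), power at 5% is 29%.

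**Pattern of significance under a constant effect.** The four visit statistics were simulated as multivariate normal (400,000 draws), each with mean 2.81 and common correlation ρ. By construction nothing changes between visits. 'Mixed' means at least one visit significant and at least one not.

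| ρ | Mixed, 5% | Week 28 significant, Week 52 not, 5% | Mixed, 5%/4 | Week 28 significant, Week 52 not, 5%/4 |
|---|---|---|---|---|
| 0.3 | 48% | 13% | 68% | 19% |
| 0.5 | 41% | 11% | 57% | 16% |
| 0.7 | 32% | 9% | 44% | 12% |
| 0.8 | 26% | 7% | 35% | 10% |
| 0.9 | 18% | 5% | 25% | 7% |

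The mirror-image error, Week 16 not significant and Week 28 significant, occurs equally often.

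**Direct contrast between two visits.** SE = 1.92 × √(2(1 - ρ)); the 95% half-width is 1.96 × SE.

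| ρ | SE | 95% half-width | Power, full loss (5.4) | Power, half loss (2.7) |
|---|---|---|---|---|
| 0.3 | 2.28 | 4.46 | 66% | 22% |
| 0.5 | 1.92 | 3.77 | 80% | 29% |
| 0.7 | 1.49 | 2.92 | 95% | 44% |
| 0.8 | 1.22 | 2.39 | 99% | 60% |
| 0.9 | 0.86 | 1.69 | >99% | 88% |

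At ρ of 0.5 or more, the contrast is at least as precise as a single-visit effect, and the planned 168 patients give 80% power or better to detect complete loss. Below 0.5 it is less precise.

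**The case against.** A reader might infer that the investigators will read onset and persistence from which visits reach significance. The article does not say so. It gives no reading rule, and ANCOVA yields an estimate and interval at each visit that could describe the curve informally. The misreading rates above therefore show what such a rule would do; they do not describe a stated procedure. This objection stands.

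A reader might also infer that the plan cannot address Question 3. That goes too far. One ordinary sense of persistence is whether patients are still better than placebo after treatment stops, and the between-arm differences at Weeks 40 and 52 answer that. A Week 52 minus Week 28 contrast alone would not. The plan is incomplete for this question, not mismatched to it.

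Three further points have weight. The text does not call the analyses separate or exclude a joint model, although LOCF with ANCOVA makes visit-by-visit fitting the natural reading. The full protocol and SAP are not shown and may contain contrasts. And the mixed-pattern rate includes outcomes, such as a lone miss at Week 40, that nobody would call delay or loss; the specific false loss at Week 52 is much rarer.

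Nor does the contrast resolve everything. At ρ = 0.5 its power for a half-loss (29%) equals that of a single-visit test of a half-sized effect.

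What remains is that the article does not leave the method open. It commits to a method, covariate, missing-data rule and error correction, and none of these estimates the change in effect that part of its own question concerns.

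**Conclusion.** The point holds as a gap in the stated analysis. The per-visit ANCOVA tells whether a benefit is present at each visit; nothing stated estimates build-up or fading, and no rule links the results to a conclusion on onset or persistence.

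The size of the risk depends on a reading by significance, which the text does not state, and on an assumed correlation. At 0.5–0.8 and an uncorrected 5%, a constant effect gives the false loss at Week 52 in 7–11% of trials and a mixed pattern in 26–41%. Under four-visit Bonferroni these rise to 10–16% and 35–57%.

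No number in the article is wrong, and neither the sample size nor the end-of-treatment comparison is affected. Severity is minor to moderate.

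**What to change.** Keep the between-arm effect at each visit to show whether a benefit is present, but obtain all of them from one repeated-measures model over Weeks 16, 28, 40 and 52 with treatment-by-visit and baseline-by-visit terms.

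For Question 3, prespecify these contrasts of the treatment effect, each with a 95% confidence interval:

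- Week 28 minus Week 16 (build-up)
- Week 40 minus Week 28 (early persistence)
- Week 52 minus Week 28 (late persistence)

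State that conclusions about build-up or fading rest on these estimates and intervals, not on the pattern of significant visits. Where an interval is compatible with both full retention and substantial loss, report the time course as unresolved.

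Fit the contrasts to observed scores. If LOCF values are used, a patient who leaves after Week 28 contributes zero change from Week 28 by construction, which can imitate persistence.

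The cost is some added wording in the analysis plan and a little more analysis, with no extra patients, visits or measurements. The downside is that the contrasts may show the time course to be only partly resolved.
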